## Outcome measures, data collection, and data management

###  1 st phase – intervention development

Information recorded will include gender, age, place of residence (urban vs. rural), and usage of digital devices and the internet for all workshop participants, as well as the respective healthcare professionals’ professions.

### 2nd phase - pre-testing of the intervention

The pretest of the intervention (usability test) will be based on observations of the participants using the think-aloud method. We will document observations in an observation protocol, which will record the comments made as part of the think-aloud process. The gender, age, and previous digital experience of the participating patient and physiotherapist will also be recorded. A digital audio recording will be made with the consent of all participants. Furthermore, participants will rate the technical components using a traffic light system and record expected benefits.

### 3rd phase - pilot study and evaluation

During piloting of the intervention, data for outcomes and other variables will be collected continuously (e.g. recruitment rates, content and duration of physiotherapy and tablet use) or at three measurement points: at baseline (T0), after 12 weeks (T1, end of physiotherapy treatment), and after 20 weeks (T2, follow-up). An overview of the different primary and secondary outcome variables is provided in Tables 1 and 2.

**Table 1 Tab1:** Primary feasibility outcomes

Outcome	Definition/measurement	Data source	Success threshold
Recruitment rate patients	Proportion of patients approached who meet the eligibility criteria and agree to enter the study; Reasons for agreement or disagreement	Recruitment protocol general practitioner; interview with patients and general practitioner at T2^c^	> 50%
Recruitment rate professionals	Proportion of physiotherapist and general practitioners approached who agree to enter the study; Reasons for agreement or disagreement	Recruitment protocol study team; interview with physiotherapists and general practitioner at T2^c^	> 30%
Completion rate	Proportion of all study patients that remain participants until the end of the defined study period	Study management protocol	≥ 95%
Compliance with the intervention	Proportion of all patients who receive a scheduled, individually digital exercise plan	Documentation physiotherapist	100%
	Proportion of all patients who used the tablet for exercise at least one day per week; content and duration of each tablet usage	Tablet user data	≥ 80%
	Proportion of all patients who used the tablet for gaming at least one day per week; content and duration of each tablet usage	Tablet user data	≥ 80%
	Proportion of perceived video calls that were suggested by the PT; content and duration of each physiotherapy session	Documentation physiotherapist	≥ 80%
Compliance with study procedures	Proportion of complete data	Study management protocol	≥ 90%
	Proportion of participants who rate assessments as feasible to use	Interview with patients, physiotherapists and general practitioners at T2^c^	≥ 80%
	Proportion of participating professionals who rate the study procedures as feasible		≥ 80%
	Proportion of participants who use the supporting materials provided by the study team		≥ 80%
Acceptability	Views and experience of the intervention, amount of perceived barriers and facilitators	Interview with patients, physiotherapists and general practitioners at T2^c^	Not applicable
	Attitude and experience with modern technology	Patient questionnaire at T0^a^, T1^b^ and interview at T2^c^	

^a^*T0*: baseline assessment

^b^*T1*: 12-week follow-up (end of physiotherapy)

^c^*T2*: 20-week follow-up

**Table 2 Tab2:** Secondary patient-related outcomes

Outcome	Instrument	Data source	Measurement point
Balance, walking speed, strength of the lower extremities	Short Physical Performance Battery, SPPB [42]	Physiotherapist	T0^a^, T1^b^
Physical activity in everyday life and sporting activities, including facilitators and barriers to physical activity adherence, and the intention to carry out regular physical activity (at least 30 min on at least 5 days a week)	Freiburg Physical Activity Questionnaire, FFB [46] and additional items	Patient-reported via questionnaire (T0, T1) or interview (T2)	T0, T1, T2^c^
Activities of daily living	Hannover Functional Ability Questionnaire (FFbH) [47]		T0, T1
Quality of life and well-being	Short-Form Health Survey, SF-8 [43]		T0, T1
Social situation and social contacts	Social Situation (Part 1), SoS [45]		T0, T1
Falls and fall-related treatment	Fall assessment, self-generated items		T0, T1

^a^*T0*: baseline assessment

^b^*T1*: 12-week follow-up (end of physiotherapy)

^c^*T2*: 20-week follow-up

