#### Sample size calculation

A formal sample size power calculation is not appropriate for this feasibility study as the outcomes were the feasibility and acceptability of the intervention rather than effectiveness [36]. Accordingly, the sample size was chosen primarily to estimate key feasibility parameters with acceptable precision and to inform the design of a future definitive trial. The selected sample size of 60 patients, including 30 participants in the intervention group, is consistent with published recommendations for pilot and feasibility studies [37–39]. For example, a sample of 30 participants in the intervention group allows estimation of key proportions such as adherence, intervention uptake, and study completion with sufficient precision to judge whether predefined feasibility criteria are likely to be met and to identify major implementation problems. The chosen sample is therefore intended to support estimation of recruitment, retention, adherence, acceptability, and data completeness, rather than formal hypothesis testing. A review of studies on data saturation in qualitative research indicates a sample of 9–17 interviews as sufficient to achieve saturation [40]. Therefore, the selected sample of 60 patients should provide sufficient information about the feasibility and acceptability of the intervention.

As physiotherapists are already characterised by a high workload, we assume that no more than two additional study patients per therapist can be treated at the same time. In this respect, a sample size of 30 per group also corresponds to the maximum number of patients that could be treated by five physiotherapists within 39 weeks of the intervention period of each group. It is anticipated that each general practitioner will be able to recruit two patients per month per study group over the course of a 5-month recruitment period. Consequently, two general practitioners will be required per district, with the objective of recruiting 30 patients per study arm. In order to achieve an adequate number of participants, we will regularly monitor the response rate and, if necessary, consider expanding the districts in which recruitment takes place.

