#### Intervention group

The recruitment, implementation, and evaluation of the intervention group will be started after the development and pre-testing of the intervention has been completed (= 3rd study phase; see Fig. 1). Participants in the intervention group also will receive a study-specific prescription for physiotherapy from their general practitioner. The baseline assessment (T0) will be recorded during the first physiotherapy session. After this, physiotherapy treatment will take place as a hybrid model for a maximum of 12 weeks. A hybrid model refers to a combination of online physiotherapy sessions (video therapy) and independent home exercises by the patients, with an individual digital exercise plan, based on a physiotherapeutic assessment. The physiotherapist and patient collaboratively will select exercises from a diverse portfolio to create an individualised exercise programme. The portfolio consists of exercises designed to improve coordination, balance, mobility, strength, and endurance. The exercises can be performed in a sitting or standing position, or on the floor, and are available at different difficulty levels. The physiotherapist will transfer video-based instructions for the exercises to the patient’s tablet. The selected exercises will be practiced face-to-face under therapeutic supervision during an appointment, either in the practice or at home. Patients will then carry out the selected exercises independently at home for the following 12 weeks. The physiotherapist and the patient will jointly determine the frequency of further physiotherapy sessions using video therapy (20 min each). The online sessions will be utilised to address concerns or questions, demonstrate proper exercise techniques, or discuss adjustments of the exercise plan. Video-based instructions and movement monitoring, which recognises body gestures and postures, will aid in the accurate execution of exercises. Also, face-to-face sessions will be available if needed. The physiotherapists receive an expense allowance per patient.

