Compliance with the intervention also will be assessed by analysing the physiotherapy sessions and tablet usage. For each tablet use, user data on the frequency and duration of use, as well as the services utilised, will be conducted. This comprises the use of the intervention elements, including exercises and gaming applications, as well as options for social contact. In addition, all face-to-face and online physiotherapy sessions will be documented on the physiotherapy prescription, detailing the duration, content, quality and any problems encountered during each session. No content analysis of data, such as browsing history, or image data from online sessions will be carried out. As part of the patient questionnaire, different items, based on the Unified Theory for Acceptance and Use of Technology (UTAUT) [41], will be used to measure patients’ attitude and experience with modern technology.

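### As printed, the video-therapy compliance criterion in Table 1 takes calls held as its base, so missed calls never count and it does not measure compliance

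*Protocol article*

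**What the plan says.** Table 1 of the protocol article (3rd phase, pilot study and evaluation) lists the primary feasibility outcomes. One row under compliance with the intervention reads "Proportion of perceived video calls that were suggested by the PT", and goes on to list what each physiotherapy session contained and how long it lasted. Its data source is the physiotherapist's documentation and its success threshold is at least 80%. A neighbouring row in the same block reads "Proportion of all patients who used the tablet for exercise at least one day per week", which names the base first and the qualifying event second.

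Three other places bear on the row:
- The Intervention group section leaves the frequency of video sessions to be settled jointly by physiotherapist and patient, and fixes no number.
- The Primary feasibility outcomes section under Outcome measures says that "all face-to-face and online physiotherapy sessions will be documented on the physiotherapy prescription, detailing the duration, content, quality and any problems encountered during each session".
- The Data analysis section says that the thresholds inform the reading of the results and are not strict pass-fail limits. It also plans 95% confidence intervals.

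No other section restates the video-call criterion.

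**The concern.** A compliance measure should show how much of what was planned took place. For video therapy that means calls held out of calls suggested or agreed. The printed row runs the other way: it starts from calls that took place and asks what share of them the physiotherapist had suggested. That describes who initiated the calls, not whether patients attended.

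Monitoring by video therapy is one of the five components named for evaluation in the Objectives, and this is the only Table 1 row that attaches a threshold to it. The Sample size calculation section justifies 30 intervention patients partly by the ability to judge whether feasibility criteria are met. A criterion that cannot register non-attendance does not serve that purpose for this component.

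**Working it through.** The 80% threshold is a set value, so the plan has no derived figure to reproduce. The check compares the two ratios.

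**Definitions**
- S = calls suggested by the physiotherapist
- A = suggested calls that were held
- U = calls held at the patient's request, not suggested by the physiotherapist
- Ratio as printed = A / (A + U), taking *perceived* to mean held
- Attendance ratio = A / S

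S does not appear in the printed ratio, so the missed calls (S − A) cannot affect it.

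**Inputs**
- From the document: "The selected sample size of 60 patients, including 30 participants in the intervention group", so 30 patients; threshold 80%.
- Assumed, because the document gives no figure: 6 suggested calls per patient, so S = 30 × 6 = 180. The range examined is 3 calls (S = 90) to 12 calls (S = 360) per patient. U is zero or about 30% of A.

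**Results for S = 180**

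| A | U | As printed | Attendance |
|---|---|---|---|
| 4 | 0 | 4/4 = 100%, meets | 4/180 = 2.2%, does not meet |
| 90 | 0 | 90/90 = 100%, meets | 90/180 = 50%, does not meet |
| 90 | 27 | 90/117 = 76.9%, does not meet | 90/180 = 50%, does not meet |
| 180 | 0 | 180/180 = 100%, meets | 180/180 = 100%, meets |
| 180 | 54 | 180/234 = 76.9%, does not meet | 180/180 = 100%, meets |

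**When each error arises**
- The printed ratio meets the threshold when A / (A + U) ≥ 0.80, that is, when U ≤ A/4. A false pass therefore needs at least 80% of the held calls to have been suggested by the physiotherapist.
- At full attendance (A = S = 180), a false failure arises when U > 180/4 = 45.

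**Sensitivity to the assumed number of calls.** The attendance ratio reaches 80% at 72 of 90, 144 of 180 or 288 of 360 calls. With U = 0 the printed ratio is 100% at every level of uptake above zero, for all three values of S. The direction of the fault does not depend on the assumed counts.

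**The case against.** The strongest reply is that this is a slip of wording and not a choice of analysis. *Perceived* is undefined, and reading it as held is itself an inference. The row stands under compliance, and the authors most likely meant the share of suggested calls that were attended. That is probably right, but the printed text is the operational definition of a primary feasibility outcome and nothing else in the article corrects it.

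A second reply concerns impact, and it stands. The thresholds are not binding, and the overall rating also rests on pragmatic considerations and the team's judgment. The same row collects the content and duration of every session. All intervention patients and participating physiotherapists are interviewed, with video therapy among the topics. Very low use would be visible in that material. A reader might infer that the misworded row would by itself lead to a wrong feasibility decision; the document does not support that.

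Two further inferences should be resisted:
- A reader might conclude that agreed but missed calls go unrecorded, because the article says that "all face-to-face and online physiotherapy sessions will be documented on the physiotherapy prescription" and does not mention missed ones. That is silence in a condensed article. The forms and operating procedures are not shown, so it is a matter to confirm and not a fault.
- A reader might see a contradiction between joint setting of frequency and calls suggested by the physiotherapist. There is none, since a physiotherapist can suggest calls within a jointly agreed plan. The fuller wording *suggested by or agreed with* simply covers both.

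Finally, the call counts used above are hypothetical. They illustrate the fault and do not predict what the trial will observe.

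**Conclusion.** The point holds for the row as printed. The criterion uses held calls as its base, cannot register missed or declined calls, and so does not measure compliance. If all held calls were suggested by the physiotherapist, it is 100% at any uptake above zero. If patients request more than one extra call for every four suggested calls held, it falls below 80% even at full attendance.

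This rests on reading *perceived* as held, the most plausible sense for a measure taken from physiotherapist documentation. The fault is probably one of wording and its practical effect is limited, for the reasons accepted above. It still merits correction, because the row is the only thresholded criterion for video therapy.

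**What to change.** Reword the row as: proportion of video calls suggested by or agreed with the physiotherapist that were held (intervention group, threshold at least 80%). Alongside it:
- State whether the unit is the call or the patient.
- State how patients with no agreed video calls are handled, since a per-patient ratio is undefined for them and no minimum number of calls is set.
- Leave extra calls requested by patients out of the ratio and report them separately.
- Confirm that the physiotherapist's documentation captures agreed calls that were not held.
- If calls are pooled over patients, compute the 95% confidence interval with allowance for clustering by patient, because calls from one patient are not independent.

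The cost is one reworded table row and, if missed calls are not already captured, a small addition to an existing form. Trial status says that intervention-group recruitment had not begun at submission and was planned for July 2024. If it has since started, the definition can still be corrected before analysis, but whether agreed calls were logged should be checked promptly.

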#### Primary feasibility outcomes

The primary aim of the study is to assess the feasibility and acceptability of the intervention and the study procedures. Therefore, the primary feasibility outcomes are recruitment rate, completion rate, acceptability, adherence, utilisation, and compliance with study procedures, including time requirements, resource demands, data collection, data management, and the usefulness of supporting materials (see Table 1).

In addition to the continuous recording of recruitment rates, including reasons for participation or non-participation, structural data of participating practitioners and physiotherapists will be collected, including the location of the practice (urban vs. rural), the number of employees (< 5, > 5), the average number of patients per week, the proportion of older patients (65 years or older), and experience with digitalisation (scheduling, documentation, use of video therapy, or electronic patient records). Furthermore, patients’ technical requirements are documented, including the presence of a television and a PC or tablet, access to the Internet, and technical experience.

Acceptability and compliance with the intervention and the study procedures will be assessed with patients, physiotherapists, and general practitioners taking part in the study by obtaining their views and experience of the intervention in interviews. Qualitative interviews will be conducted with all participants from the intervention group, as well as all participating physiotherapists and general practitioners. The interview guides will address experiences of intervention use, perceived relevance and burden, usability of the technical components, experiences with video therapy, and perceived changes in physical activity and social participation. We will assess the level of intervention implementation and associated effort, as well as the acceptability of the intervention to both patients and healthcare practitioners. Furthermore, an evaluation of the helpfulness of the provided support materials will be conducted, including an assessment of the exercise overview for therapists, exercise videos, written instructions for selected exercises, and the user manual for patients. Additionally, we will examine factors that facilitate or hinder the implementation of the intervention, short- and long-term adherence, and behavioural change. The qualitative evaluation will be informed by behaviour change and implementation perspectives. Interview guides for patients and healthcare professionals will draw on UTAUT [42] and on implementation-related questions concerning capability, opportunity, and motivation to engage with the intervention and associated procedures. This theoretical orientation will support both data collection and analysis of behavioural and implementation-related barriers and facilitators.

Compliance with the intervention also will be assessed by analysing the physiotherapy sessions and tablet usage. For each tablet use, user data on the frequency and duration of use, as well as the services utilised, will be conducted. This comprises the use of the intervention elements, including exercises and gaming applications, as well as options for social contact. In addition, all face-to-face and online physiotherapy sessions will be documented on the physiotherapy prescription, detailing the duration, content, quality and any problems encountered during each session. No content analysis of data, such as browsing history, or image data from online sessions will be carried out. As part of the patient questionnaire, different items, based on the Unified Theory for Acceptance and Use of Technology (UTAUT) [41], will be used to measure patients’ attitude and experience with modern technology.

#### Secondary outcomes

Secondary patient-related outcome measures (T0, T1) are objective and subjective assessments of physical function, physical activity, cognitive function, self-care, quality of life and participation (see Table 2).

Physical function will be measured by the SPPB at baseline (T0) and at the end of the physiotherapy after 12 weeks (T1). The SPPB [42] comprises three tests by the physiotherapist: tandem stand, walk over four metres, and sit-to-stand test. Therefore, the SPPB measures deficits in mobility, muscle strength of the lower extremities and balance. The assessments of physical activity will include self-reported physical activity in everyday life and sporting activities [32], as well as facilitators and barriers to physical activity adherence, and the patient’s intention to carry out regular physical activity (at least 30 min on at least 5 days a week). Further, physical function and activities of daily living will be measured [33]. The Short-Form Health Survey (SF-8) [43, 44] will be used to measure health-related quality of life. Each of the eight dimensions of the SF-36 is represented by a single item in the SF8. The Social Situation Questionnaire of Nikolaus [45] will be used to record social situation and social contacts through several items. This includes existing social contacts and support, and social activities.

#### Additional measures

Descriptive data will be collected at baseline, including patient-reported socio-demographic information (such as age, gender, education, and living situation), data on infrastructure or previous physiotherapy in the past 6 months, and medical data reported by general practitioner (such as body weight, body height, diagnoses (ICD-10), and limitations in cognition, motor skills, mood, and participation/social situation, reason for prescribing physiotherapy).

#### Data management

All assessments at baseline (T0) and after 12 weeks physiotherapy (T1) will be performed on a paper-and-pencil basis by general practitioners, physiotherapists and patients. The assessment at 20-week follow-up (T2) will be conducted through semi-structured guided interviews by trained members of the study team, either by telephone, video call, or face to face, depending on participants’ preferences and practical considerations.

After each measurement point, the pseudonymised patient data will be transferred to the study centre via fax or upload to a secure project cloud. A copy of the questionnaires will be safely stored at the respective practice of general practitioners or physiotherapists. The pseudonymised data will be stored on a secure computer and will be handled in accordance with the data protection declaration. All hard-copy printouts will be destroyed once the analysis is complete.

The study team will perform data entry and analysis. All data will be entered into a database and validated through double entry. Additionally, the data will be checked for inconsistencies and completeness, and its quality will be reported to the general practitioners and physiotherapists. Data quality (e.g. proportion of missing values) and organisational or logistic issues will be reviewed and discussed in weekly team meetings. In this way, necessary actions to improve data quality and study logistics can be taken in good time. In addition, training on data entry will be carried out to ensure data quality.

